**7.0 STUDY PROCEDURES/EVALUATIONS**

**7.1 Clinical Evaluations and Procedures**

See Appendix I for a complete Schedule of Procedures and Evaluations by study visit.

Interested volunteers will contact the study staff to discuss study details, including inclusion criteria, prior to the screening visit. Potential participants will be screened for presumptive eligibility for the study according to the procedures described below. All procedures will be completed in a step-wise manner for potential participants who meet the study eligibility criteria. For participants who do not meet the eligibility criteria, screening will be discontinued when ineligibility is determined. For potential participants who are found to be presumptively eligible at this visit, final eligibility will be confirmed at an Enrollment Visit scheduled to take place 2-6 days following the next menses within 30 days of the Screening Visit.

## Screening Visit

## Clinical Procedures

- Obtain informed consent.
- Assign Participant ID.
- Collect demographic and locator information.
- Collect medical history and concomitant medication information.
- Collect blood for pregnancy test, HIV EIA, RPR, herpes serology
- Collect urine for HCG pregnancy test; provide participant with result.
- Collect urine for microscopy and culture.
- Perform pelvic examination including:
- Speculum examination of vagina and cervix,
- Collection of pH sample from the vaginal wall, anterior and posterior fornices,
- Swabs from anterior or lateral fornix for wet mount (two samples of discharge on slide for saline prep, potassium hydroxide prep and whiff test), & p30 test for detection of semen (One-Step ABA card PSA, Abacus Diagnostics, West Hills, CA).
- Collection of baseline CVL,
- Pap test (if documentation of a negative result within the past year is not available),
- Cervical swab for *N. gonorrhoeae* and *C. trachomatis*,
- If ulcerative lesions are noted, collect swab for herpes simplex virus culture,
- Colposcopically directed cervical biopsy.
  - If participant determined to be ineligible, end visit and complete all required data collection forms. If participant remains presumptively eligible, schedule Enrollment Visit to occur 2-6 days following menses within 30 days after the Screening Visit.
- Instruct participant not to use vaginal products and to abstain from vaginal and anal intercourse for 48 hours prior to the Enrollment Visit.
- Complete all required data collection forms.

### Laboratory Procedures

- Record results of serum and urine pregnancy tests.
- Record results of urine microscopy and culture.
- Record vaginal pH measurements.
- Examine wet mount by direct microscopy to detect *T. vaginalis*, *C. albicans* infections, and clue cells for BV. Perform whiff test.
- Conduct p30 test for detection of semen.
- Conduct tests for *N. gonorrhoeae* and *C. trachomatis*.
- Read and record Pap test results.
- Conduct culture of swab for HSV, if clinically indicated.
- Conduct serology for RPR with confirmation by FTA-ABS or TPHA for *T. pallidum.*
- Conduct type-specific herpes serology.
- Conduct EIA test for HIV.
- Process, spin, measure volume, aliquot and freeze CVL supernatants, which will be used for assessment of endogenous antimicrobial activity, cytokines, chemokines and mediators of mucosal immunity.
- Process cervical biopsy tissue for assessment of epithelial integrity by microscopy and qRT-PCR.

Enrollment Visit (Day 0)

Participants who are found to be presumptively eligible at their Screening Visits will complete Enrollment Visits within 30 days after the Screening Visit. In order to ensure a minimum of 21 days without menstrual bleeding, participants will be scheduled for an Enrollment Visit 2-6 days after the next menstrual period ends. Participants who do not complete an Enrollment Visit within 30 days of screening must repeat the screening process in order to participate. All participants will receive their screening test results at their Enrollment Visits. For those whose test results meet the study eligibility criteria, the procedures below will be undertaken in a step-wise manner to confirm eligibility. As was the case at the Screening Visit, the procedures will be discontinued if ineligibility is determined at this visit.

## Clinical Procedures

- Update locator information.
- Review interim medical history and concomitant medication information.
- Provide participant with screening test results.
- Collect urine for HCG pregnancy test; provide participant with result.
- Perform pelvic examination including:
- Speculum examination of vagina and cervix,
- Collect pH sample from the vaginal wall, anterior and posterior fornices,
- Gently swab anterior or lateral fornix for wet mount (two samples of discharge on slide for saline prep, potassium hydroxide prep, whiff test, and microscopic inspection for sperm) and p30 test for detection of semen,
- Collect vaginal swab for evaluation of vaginal flora,
- Collect cytobrush.
- If patient determined to be ineligible, end visit and complete all required data collection forms. If participant remains eligible, randomize/assign Enrollment ID and continue.
- Distribute study supplies, including thirty (30) single-application tubes of Acidform gel or placebo gel and 30 single-use applicators, study diary, application and storage instruction sheet (Appendix III) and panty liners.
- Instruct participants to bring study diary and used and unused tubes of gel to all follow-up visits.
- Provide information regarding product administration.
- Provide guidance for the administration of the first dose of study gel by the participant.
- Measure vaginal pH and collect CVL 2 hours post-application of Acidform or HEC.
- Instruct participant on anticipated amount, consistency and color of discharge due to gel expulsion.
- Instruct participant on proper gel insertion techniques and supply storage.
- Instruct participant to apply a dose at bedtime and then twice daily starting the next morning.
- Schedule Day 7 Study Visit.
- Instruct participant to not apply a dose on the morning of the Day 7 Visit. The dose will be applied after the study visit to avoid the effects of residual drug on study samples.
- Complete all required data collection forms and record any AE information.

## Laboratory Procedures

- Record results of urine pregnancy test.
- Record vaginal pH measurements prior to application of Acidform or HEC.
- Examine wet mount by direct microscopy to detect *T. vaginalis*, *C. albicans* infections, clue cells for BV, and/or sperm and record results. Perform whiff test and record results.
- Conduct p30 test for detection of semen.
- Store vaginal swabs for vaginal flora assessment. Swabs will be batched and sent to [name] at the University of Washington at the end of the study.
- Record vaginal pH 2 hours post-application of Acidform or HEC.
- Process, spin, measure volume, aliquot and freeze CVL supernatants for spiking studies.
- Process cytobrush for evaluation of cell populations by FACS.

## Follow-up Visit (Day 7)

A subsequent visit will be scheduled after 5-9 days of product dosing (target Day 7). Every attempt will be made to schedule appointment after 7 days of dosing to ensure adequate exposure. If a participant has discolored or malodorous vaginal discharge or suspected cervicitis at any Study Visit, an appropriate clinical and laboratory work-up will be conducted (see Appendix IV). If a participant has a genital ulcer, tests will be conducted for syphilis or herpes simplex as appropriate. Continuation in the study will be based on the severity of the abnormality noted as described in Appendix IV.

## Clinical Procedures

- Update locator information.
- Review interim medical history, AE information, and concomitant medication information.
- Review daily study records, note the time of last application of the product, and conduct adherence review.
- Count and record the number of used and unused tubes and dispose of used tubes in accordance with the guidelines.
- Perform speculum exam including
- Visual inspection of vagina and cervix,
- pH sample from vaginal wall, anterior and posterior fornices,
- Swabs for wet mount and p30 test for detection of semen,
- CVL collection.
- If abnormalities are noted, refer to Appendix IV for procedures to be followed.
- Schedule Study Visit for Day 14 and complete all required data collection forms.
- Review applicator instructions, remind participant to abstain from vaginal and anal intercourse and remind participant to continue twice daily dosing.
- Instruct participant to not apply a dose on the morning of the Day 14 Visit. The dose will be applied after the study visit to avoid the effects of residual drug on study samples.
- Instruct participant to bring used and unused products to the next visit.

## Laboratory Procedures

- Record vaginal pH measurements.
- Examine wet mount by direct microscopy to detect *T. vaginalis*, *C. albicans* infections, clue cells for BV, and/or sperm. Perform whiff test and record results.
- Conduct p30 test for detection of semen.
- Process, spin, measure volume, aliquot and freeze CVL supernatants.

## Follow-up Visit (Day 14)

A subsequent visit will be scheduled after 12-15 days of product dosing (target Day 14). Every attempt will be made to schedule appointment after 14 days of dosing to ensure adequate exposure. If a participant has discolored or malodorous vaginal discharge or suspected cervicitis at any Study Visit, an appropriate clinical and laboratory work-up will be conducted (see Appendix IV). If a participant has a genital ulcer, tests will be conducted for syphilis or herpes simplex as appropriate. Continuation in the study will be based on the severity of the abnormality noted as described in Appendix IV.

## Clinical Procedures

- Update locator information.
- Review interim medical history, AE information, and concomitant medication information.
- Review daily study records, note the time of last application of the product, and conduct adherence review.
- Count and record the number of used and unused tubes and dispose of used and/or remaining tubes in accordance with the guidelines.
- Perform speculum exam including
  - Visual inspection of vagina and cervix,
  - pH sample from vaginal wall, anterior & posterior fornices,
  - Swabs for wet mount, vaginal flora and p30 test for detection of semen,
  - CVL collection,
  - Cytobrush collection,
  - Colposcopically directed cervical biopsy.
- If abnormalities are noted, refer to Appendix IV for procedures to be followed.
- Schedule Final Visit 3-8 days later.
- Complete all required data collection forms.
- Remind participant to abstain from vaginal and anal intercourse.

## Laboratory Procedures

- Record vaginal pH measurements.
- Examine wet mount by direct microscopy to detect *T. vaginalis*, *C. albicans* infections, clue cells for BV, and/or sperm. Perform whiff test.
- Conduct p30 test for detection of semen.
- Process, spin, measure volume, aliquot and freeze CVL supernatants.
- Process cytobrush for evaluation of cell populations by FACS.
- Process cervical biopsy tissue for assessment of epithelial integrity by microscopy and qRT-PCR.
- Store vaginal swabs for vaginal flora assessment.

## Final Visit (Day 21)

## A final visit will take place 3-8 days after the final application of investigational product. This visit will mark the end of the subject’s participation in the study.

**Clinical Procedures**

- Update locator information.
- Review interim medical history, AE information, and concomitant medication information.
- Review daily study records.
- Perform speculum exam including
  - Visual inspection of vagina and cervix,
  - pH sample from vaginal wall, anterior & posterior fornices,
  - Swabs for wet mount, vaginal flora and p30 test for detection of semen,
  - CVL collection,
  - Cytobrush collection.
- If abnormalities are noted, refer to Appendix IV for procedures to be followed.
- Complete all required data collection forms.
- Complete Termination Form.

## Laboratory Procedures

- Record vaginal pH measurements.
- Examine wet mount by direct microscopy to detect *T. vaginalis*, *C. albicans* infections, clue cells for BV, and/or sperm. Perform whiff test.
- Conduct p30 test for detection of semen.
- Process, spin, measure volume, aliquot and freeze CVL supernatants.
- Process cytobrush for evaluation of cell populations by FACS.
- Store vaginal swabs for vaginal flora assessment.

## 7.2 Interim Contacts and Visits (ad hoc)

Interim contacts and visits may be performed at participant request at any time during the study. All interim contacts and visits will be documented in participants' study records and on applicable case report forms.

Some interim visits may occur for administrative reasons (for example, the participant may have questions for study staff). Interim visits may also occur in response to AEs experienced by study participants.

When interim contacts or visits are completed in response to participant reports of AEs, study clinicians will assess the reported event clinically and provide or refer the participant for appropriate medical care.

**7.3 Specimen Preparation, Handling and Shipping**

Unused drug will be shipped to Instead Healthcare, LLC and vaginal swabs for assessment of vaginal flora will be shipped to [name] at the Fred Hutchinson Cancer Research Center at the University of Washington in accordance with IATA specimen shipping regulations.

**7.4 Biohazard Containment**

## Appropriate blood and secretion precautions will be employed by all personnel in the drawing of blood and shipping and handling of all specimens for this study, as currently recommended by the U.S. Centers for Disease Control and Prevention (CDC). Universal precautions will be observed at all times.

**8.0 ASSESSMENT OF SAFETY**

**8.1 Adverse Events**

The Female Genital Grading Table for Use in Microbicide Studies will be the primary tool for grading adverse events for this protocol and is available on the RCC website at http://rcc.tech-res-intl.com/eae.htm. AEs not included in that table will be graded using the Division of AIDS Table for Grading the Severity of Adult and Pediatric Adverse Events (DAIDS AE Grading Table), Version 1.0, December 2004. In cases where an AE is covered in both tables, the Female Genital Grading Table will be the grading scale utilized. Study staff will document on case report forms all AEs reported by or observed in enrolled study participants regardless of severity and presumed relationship to study product. All AE reports should contain the date the AE occurred, a brief description of the event, the time of onset, the duration of the event, the severity, the treatment required (if any), the relationship to study drug, the study drug action taken, the outcome, and whether or not the AE is Serious. The investigator or designee will assess the relationship of all AEs to the study product based on prior clinical studies, the Investigator’s Brochure, and his/her clinical judgment.

Acidform gel has 510K clearance from the FDA for use as a lubricant. This puts adverse event reporting for the study agent under device regulations. The investigator shall submit to the reviewing IRB, Safety Committee, NIAID Medical Officer, and the Center for Devices and Radiological Health (CDRH) a report of any unanticipated adverse device effect (UADE) occurring during the study as soon as possible, but in no event later than 10 working days after the investigator first learns of the effect. Unanticipated adverse device effect means any serious adverse effect on health or safety or any life-threatening problem or death caused by, or associated with, a device, if that effect, problem, or death was not previously identified in nature, severity, or degree of incidence in the investigational plan or application (including a supplementary plan or application), or any other unanticipated serious problem associated with a device that relates to the rights, safety, or welfare of subjects. For reporting to CDRH, the contact information is:

[name]

POS/IDE, HFZ-401

FDA, CDRH

[name]

[name]

**8.2 Local regulatory requirements**

Information on all AEs experienced by study participants will be included in reports to the DAIDS Medical Officer. Study staff will report information on AEs to the AECOM IRB and GCRC in accordance with all applicable regulations and site-specific requirements.

As required by New York State law, all positive results for chlamydia, gonorrhea, HIV and syphilis will be reported to the New York City and State Departments of Health.

**8.3 Social harms reporting**

Participants may become embarrassed, worried, or anxious when completing their HIV risk assessment and/or receiving HIV counseling. They also may become worried or anxious while waiting for their HIV test results. Trained counselors will be available to help participants deal with these feelings.

Although the study site will make every effort to protect participant privacy and confidentiality, it is possible that participants' involvement in the study could become known to others, and that social harms may result (i.e., because participants could become labeled as HIV-infected or at "high risk" for HIV infection). For example, participants could be treated unfairly or discriminated against, or could have problems being accepted by their families and/or communities.

Women in abusive relationships may be unable to avoid sexual activity due to risk of physical harm. The study team will carefully inquire whether participants are able to decline intercourse and will not enroll any subjects who are evasive or uncertain in their responses.

## 9.0 CLINICAL MANAGEMENT

**9.1 Toxicity Management**

In response to AEs reported by study participants and/or observed upon exam by study staff, the study site investigator or designee will recommend either continuation or holding gel use consistent with the criteria in Appendix IV.

**9.2 Other Disease Events**

Study staff will comply with all applicable local requirements to report communicable diseases including HIV and other reportable STI identified among study participants and their partners (if obligated by local law) to local health authorities. Participants will be made aware of all reporting requirements during the study informed consent process. As required by New York State law, all positive results for chlamydia, gonorrhea, HIV and syphilis will be reported to the New York City and State Departments of Health.

**9.3 Pregnancy**

If a participant is found to be pregnant at the screening or enrollment visits, she will discuss the results with the clinician and will not continue in the study. She will be referred for care by the study clinicians. If she becomes pregnant during the course of the study, she will discontinue study product and be referred for care. The study team will attempt to obtain pregnancy outcome data on any women who become pregnant while on study drug.

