# 5.1 Participant Inclusion Criteria

# Women who meet all of the following criteria (by self-report, unless otherwise specified) are eligible for inclusion in this study:

- Age between 18 and 50.
- Able and willing to provide written informed consent to participate in the study.
- Normal menstrual history with regular cycles with a minimum of 21 days between menses.
- Low risk for HIV/STI infection. Low risk is defined as

1. Not having had an STI in the last 6 months.
2. Not having used non-therapeutic intravenous drugs in the last year.
3. Being either sexually abstinent or being in a stable, mutually monogamous relationship with a partner who is not known to be HIV positive.

- Agree to the insertion of Acidform lubricant or HEC gel.
- Agree to abstain from vaginal and anal intercourse and to not use vaginal products for 48 hours prior to enrollment and for the duration of the study (through the Final Visit).

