# 5.2 Exclusion Criteria

Women who meet any of the following criteria (by self-report, unless otherwise specified, at screening, enrollment, or at anytime during participation, unless otherwise specified) will be excluded from this study:

- Are pregnant (based on a serum or urine pregnancy test) or less than 6 months post-partum.
- Are currently breastfeeding.
- Are menopausal.
- Are currently using hormonal contraception or have used hormonal contraception in the previous 2 months.
- Are currently menstruating (at screening or enrollment visits – may be eligible for deferment).
- Are currently participating in a research study of other vaginal products.
- Have a positive HIV test at screening.
- Have a urinary tract infection at screening (may be eligible for re-screening after treatment).
- Have a positive chlamydia, gonorrhea, or trichomonas result at screening.
- Have an abnormal Pap test (if documentation of a negative result within the past year is not available).
- Have a clinically detectable genital abnormality (i.e., vulvar, vaginal, cervical and/or perianal ulcer and/or lesion or an abnormal wet mount).
- Have a history of intermenstrual bleeding in the 3 months prior to enrollment.
- Have had gynecological surgery or received treatment for syphilis, genital herpes, chlamydia, gonorrhea, trichomonas, or genital warts in the last 6 months.
- Have received treatment for candida, bacterial vaginosis, or urinary tract infection in the prior month.
- Have douched or used any vaginal products**,** including lubricants, feminine hygiene products, vaginal drying agents and sex toys during the 48 hours prior to enrollment.
- Have had vaginal or anal intercourse during the 48 hours prior to enrollment.
- Oral or intravenous antibiotics in the 7 days prior to enrollment.

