**9.6 Criteria for Permanent Treatment Discontinuation for an Individual Participant**

The criteria for permanent treatment discontinuation of further study product/intervention(s) for an individual participant are:

- Treatment-related toxicity (see section 9), including pelvic inflammatory disease, deep epithelial disruption
- Requirement for prohibited concomitant medications such as oral or intravenous antibiotics
- Pregnancy or breastfeeding
- Completion of treatment as defined in the protocol
- Request by participant to terminate treatment
- Clinical reasons believed life-threatening by the physician even if not addressed in the toxicity section of the protocol
- Unwillingness or inability to remain abstinent for the duration of the study.

The participant will continue to be followed with participant’s permission if study product/intervention(s) is discontinued.

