**Appendix I. Schedule of assessments**

|  | **Screening** | **Enrollment**  **(Day 0)** | **Day 7**  **(Day 5-9)** | **Day 14**  **(Day 12-15)** | **Final Visit (Day 21)**  **(Day 16-21)** |
| --- | --- | --- | --- | --- | --- |
| Informed Consent | X |  |  |  |  |
| Sexual History | X | X*b* | X*b* | X*b* | X*b* |
| Medical History/Concomitant Meds | X | X*b* | X*b* | X*b* | X*b* |
| HIV EIA with confirmation | X |  |  |  |  |
| Provide HIV/STI pre-test counseling | X |  |  |  |  |
| Provide HIV/STI test results and post-test counseling |  | X |  |  |  |
| Urine Microscopy/Culture | X |  |  |  |  |
| Urine pregnancy test | X | X |  |  |  |
| Serum pregnancy test | X |  |  |  |  |
| Pelvic Exam | X | X | X | X | X |
| Pap test*c* | X |  |  |  |  |
| Vaginal pH | X | X | X | X | X |
| Wet Mount (*Trichomonas*, *Candida*, BV) | X | X | X | X | X |
| Herpes simplex virus culture | X*a* | X*a* | X*a* | X*a* | X*a* |
| ABAcard p30 test for detection of semen | X | X | X | X | X |
| *N. gonorrhoeae/C. trachomatis* | X | X*a* | X*a* | X*a* | X*a* |
| *T. pallidum* (RPR) with confirmation | X |  |  |  |  |
| Herpes simplex virus serology | X |  |  |  |  |
| CVL collection | X | X | X | X | X |
| Cytobrush collection |  | X |  | X | X |
| Vaginal swab to assess vaginal flora |  | X |  | X | X |
| Cervical biopsy | X |  |  | X |  |
| Record Adverse Events |  | X | X | X | X |
| Distribute study supplies |  | X |  |  |  |
| Distribute Participant Diary |  | X |  |  |  |
| Review Participant Diary |  |  | X | X | X |
| Count used & unused supplies |  |  | X | X |  |

*a*If clinically indicated

*b*Interim history collected

cA Pap test will be obtained if documentation of a negative result within the last year is not available

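### No pregnancy test is scheduled after Enrollment, although the protocol requires action on an on-study pregnancy: a minor missing precaution

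*Protocol*

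**What the plan says.** Section 9.3 covers a pregnancy that arises on study: "If she becomes pregnant during the course of the study, she will discontinue study product and be referred for care". It continues: "The study team will attempt to obtain pregnancy outcome data on any women who become pregnant while on study drug". Section 9.6 lists pregnancy among the reasons for permanent treatment discontinuation, and section 9.7 among those for leaving the study. Section 5.2 applies its exclusions, pregnancy included, "at screening, enrollment, or at anytime during participation, unless otherwise specified".

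In Appendix I the row "Urine pregnancy test" is marked at Screening and Enrollment only, and the serum test at Screening only. The section 7.1 lists for Day 7, Day 14 and the Final Visit include neither urine collection nor an hCG test. In the same table, gonorrhea/chlamydia testing and herpes culture carry the footnote "If clinically indicated" at the later visits. The pregnancy rows carry no such mark.

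On who may enroll, one option under low risk in section 5.1 is "Being either sexually abstinent or being in a stable, mutually monogamous relationship with a partner who is not known to be HIV positive", and section 5.2 excludes women who "Are currently using hormonal contraception or have used hormonal contraception in the previous 2 months". No other contraception is required. Abstinence runs from 48 hours before Enrollment through the Final Visit, and section 9.6 stops product for "Unwillingness or inability to remain abstinent for the duration of the study".

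**The concern.** The protocol fixes what to do about an on-study pregnancy but schedules nothing after Day 0 that would reveal one. Abstinence lowers the risk without removing it. Intercourse before the 48-hour window breaks no rule, these women use no hormonal contraception, and a conception just after Day 0 cannot show on the Day 0 test. The Final Visit is placed before the expected menses and ends participation, so a missed period, the natural prompt, would usually come after the woman has left.

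At stake are timely referral and the outcome data that section 9.3 says the team will seek. The Day 14 biopsy and any remaining doses are secondary.

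**Working it through.** **1. Tests against visits.** Before dosing: 2 urine tests and 1 serum test. After Enrollment: 0 tests at 3 visits (Day 7, Day 14, Final Visit). Appendix I and section 7.1 agree.

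**2. What the later visits do check.** Interim medical and sexual history, the diary (which records vaginal penetration), wet mount for sperm and a p30 swab. The last two look for recent semen, not pregnancy. Section 6.4 puts p30 detection at 2 days at most, while scheduled visits are about 7 days apart. Under section 6.4, product stops for sexual non-adherence only after more than one occasion. A single detected breach is recorded and no pregnancy test is prescribed.

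**3. Can conception occur without a breach?** The biological inputs are assumptions, not figures from the protocol: sperm survival up to 5 days, luteal phase 12 to 16 days (14 in the example), cycles of 26 to 28 days.
- Last permitted intercourse is Day -2, so the latest such conception is -2 + 5 = Day 3.
- Enrollment falls k = 2 to 6 days after menses ends. With menses lasting m days, ovulation is on study day (cycle length - luteal phase) - m - k.
- 28-day cycle, k = 6: 28 - 14 - 6 - m = 8 - m, which is Day 3 or earlier if m is 5 or more. 26-day cycle, k = 6: 6 - m, which is Day 1 for m = 5.
- 28-day cycle, k = 2: 12 - m, which would need m of 9 or more.

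The route is therefore open mainly to women enrolled late in the 2-6 day window. It is narrow, but it does not need an unusual cycle.

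**4. What a test could show.** Assume urine hCG turns positive 10 to 14 days after conception.
- Conception on Days 0-3 turns positive between Day 0 + 10 = Day 10 and Day 3 + 14 = Day 17. The Day 14 window (Days 12-15) lies inside that span, so the Day 14 test is early.
- Conception on Days 0-3 puts the next menses due between 0 + 12 = Day 12 and 3 + 16 = Day 19. The Final Visit (Days 16-21, before expected menses) is then pulled toward its early end. A test before expected menses falls within one luteal phase of ovulation (12 to 16 days), close to the assumed 10 to 14 day lag.
- At best, a Final Visit test on Days 16-21 reaches conceptions up to 16 - 10 = Day 6 through 21 - 10 = Day 11.

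These inputs do not support a detection percentage.

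**5. Doses left at the Day 14 visit.** Sections 6.3 and 6.4 give 2 + 2 x 13 = 28 doses. On that count, 2 + 2 x 11 = 24 are used before a Day 12 visit and 4 remain. It would leave none at a Day 14 visit, but sections 4.0 and 6.4 tell women to apply that morning's dose after the visit, and section 6.4 allows make-up days. At least the post-visit dose, plus any make-up doses, can remain. The Final Visit comes 3-8 days after the last dose, so a test there cannot trigger the product stop.

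**The case against.** The strongest reply is that nothing here is an error. Section 9.3 says what happens if pregnancy occurs and promises no periodic testing; outcome data are a best effort. No text bars a clinician from testing, and ad hoc visits are allowed. The risk is controlled by three negative tests before dosing, required abstinence, not enrolling women who are evasive or uncertain about being able to decline intercourse (section 8.3), exclusion for sperm or a positive p30 at Enrollment, and repeat checks at every visit. Enrollment soon after menses also leaves few days of permitted intercourse. If menses comes at Day 21 or later, as section 7.1 intends, ovulation falls at about Day 5 to 9 or later (21 - 16 and 21 - 12), past the Day 3 limit.

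Much of this stands. It makes the risk very small and limits the point to an inexpensive improvement. It does not close the gap: late enrollment in an ordinary cycle still permits ovulation around Days 1-3, and the semen checks cannot show pregnancy.

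A reader might go further and infer that section 9.3 contradicts Appendix I, or that the wording of section 5.2 obliges testing at every visit. The documents do not support either. A rule for an event is not a testing schedule, and the negative test before the Screening and Enrollment exams is an eligibility gate that is not stated to apply at Day 14. Nor do the documents state a specific harm of either gel, or of the biopsy, in early pregnancy.

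**Conclusion.** The point holds as a minor missing precaution. The protocol requires product stop, referral and an attempt at outcome follow-up, but schedules no test after Enrollment that would show a pregnancy. The number of pregnancies to expect among 36 women cannot be derived from the documents and is very small. No endpoint, sample size or power figure is affected.

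A reader might infer that a Final Visit test would catch nearly every such case, or that no dosing is left to stop at Day 14. Neither follows. Final Visit sensitivity is limited by its place before expected menses, and some doses can remain at Day 14. The main gain is ascertainment and referral. The finding that no test is scheduled rests on the protocol alone; the timing of conception and of a positive test rests on the assumptions labelled above.

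**What to change.** In Appendix I and section 7.1, add the urine hCG test that Appendix II already lists at the GCRC:

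1. at the Final Visit for every woman (the main change);
2. at Day 14 before the exam, with no biopsy and no further dosing if positive;
3. after any positive p30, sperm on wet mount or reported intercourse, repeated at the Final Visit.

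Name these in section 9.3 as the scheduled means of detection, and state there that a negative result does not exclude a recent conception. Care after a positive result stays as section 9.3 has it.

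Cost: 36 tests for the Final Visit alone, or 36 x 2 = 72 with Day 14, plus a few prompted tests and any for replacement participants, all at visits already planned. The price is an occasional early positive to follow up and some missed early conceptions. No endpoint or analysis changes.
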